### Approach for withdrawals, missing data and outliers

Data up to the point of withdrawal will be used for those participants who have withdrawn from the study unless they have withdrawn their consent for use of their data. No imputation will be performed for missing data. We do not plan to exclude outliers from the analysis.

### Protocol deviations

Participants will be included in the intention-to-treat analysis, regardless of protocol deviations.

### Covariates and potential confounders

Adjusted and unadjusted results will be presented for all outcomes. The results will be adjusted for:

- Gestational age at randomisation (continuous variable).

Additional baseline variables will be included in the model if these differ markedly between treatment groups and are known to influence the particular outcome.

### Multiple comparisons and multiplicity

Each of the primary outcomes will be tested at the 5% significance level. No adjustment to the significance level will be made for secondary or tertiary outcomes, subgroup analyses or sensitivity analyses. The total number of tests will be reported to allow interpretation of the risk of type I error.

### Clustering

As 20% of the ACTORDS cohort were multiple pregnancies, clustering will be accounted for in this analysis using generalised linear mixed-effects regression models with inclusion of the unique maternal identifier as a random effect to account for the nonindependence of children from multiple pregnancies.

## 11. Descriptive analysis

A flow chart will be completed to describe participant flow from randomisation to 20-year follow-up.

Summary statistics will be presented for F1 participants included in the intention-to-treat analysis, with a comparison between characteristics of those followed up and those not followed up. Baseline demographic variables will be reported as mean and standard deviation or median and interquartile range where appropriate for continuous variables and as frequency and percentages for categorical variables.

## 12. Statistical Analysis

Statistical analysis will be performed for all primary, secondary and tertiary outcomes. Analyses will compare the repeat antenatal corticosteroid (betamethasone) group to the placebo (single course) group.

Analyses for binary outcomes will be performed adjusted for covariates listed above using mixed-effects generalised linear models assuming a binary distribution and log link function, reported as relative risk (RR) with 95% confidence intervals.

Analyses for continuous outcomes will be performed adjusted for covariates listed above using mixed-effects generalised linear models assuming a normal distribution and identity function, reported as mean difference (MD) with 95% confidence intervals.

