## 3. Background: The Australasian Collaborative Trial of Repeat Doses of Steroids (ACTORDS)

### ACTORDS RCT

In this multicentre centre, two-arm, parallel, randomised double blind placebo-controlled trial, women who remained at risk of preterm birth at less than 32 weeks' gestation, 7 or more days after receiving a first course of prenatal corticosteroids, were randomly assigned to receive a repeat intramuscular dose of either betamethasone or saline placebo. This could be repeated every week the woman remained undelivered, at less than 32 weeks' gestation, if still considered to be at risk of preterm birth in the next 7 days. Primary outcomes were occurrence and severity of neonatal respiratory distress syndrome, severity of any lung disease present, use and duration of oxygen and mechanical ventilation, and weight, length, and head circumference at birth and hospital discharge.

The RCT found that fewer babies exposed to repeat corticosteroids had respiratory distress syndrome and fewer had severe lung disease than those in the placebo group. In keeping with these benefits, babies exposed to repeat corticosteroids needed less oxygen therapy, and shorter duration of mechanical ventilation. Mean weight, length, and head circumference at birth and hospital discharge did not differ between treatment groups. Z-scores for weight and head circumference at birth were lower in the babies who received repeat corticosteroids although at the time of hospital discharge Z-scores did not differ between treatment groups.

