### Subgroup analyses

Exploratory analyses for primary and secondary outcomes will investigate if the treatment effect of antenatal corticosteroid is influenced by the following variables:

- Sex
- Socioeconomic status (based on New Zealand Deprivation Index for their area of residence at 20-year follow-up) – most deprived (deciles 8-10) vs other.

Analyses for each of the primary and secondary outcomes listed will be performed with each of these potential subgroups as main and interaction effects (with treatment allocation) and measures of effect will be presented for each of the subgroup strata.

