**Addendum to statistical analysis plan for ACTORDS Follow up**

The following were added as tertiary outcomes:

- Components of functional difficulties outcome
  - Difficulty seeing, even if wearing glasses
  - Difficulty hearing, even if using a hearing aid
  - Difficulty walking or climbing steps
  - Difficulty remembering or concentrating
  - Difficulty washing all over or dressing
  - Difficulty communicating
- Components of obesity/overweight outcome
  - BMI
  - height
  - weight

This addition was made after all analyses had been completed but before unblinding of treatment groups.

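### Sex is not a pre-specified covariate for adult height, weight and BMI, which costs the height comparison precision it could have for free

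*SAP*

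**What the plan says.** - **Model.** SAP section 12: "Analyses for continuous outcomes will be performed adjusted for covariates listed above using mixed-effects generalised linear models assuming a normal distribution and identity function". Results are reported as mean differences with 95% confidence intervals. Section 10 (Clustering) adds a maternal random effect.
- **Covariates.** Section 10 (Covariates and potential confounders) lists a single item: "Gestational age at randomisation (continuous variable"). It continues: "Additional baseline variables will be included in the model if these differ markedly between treatment groups and are known to influence the particular outcome". It does not define a marked difference. It also says: "Adjusted and unadjusted results will be presented for all outcomes".
- **Use of sex.** Sex appears in section 13 (Subgroup analyses), whose scope is limited: "Exploratory analyses for primary and secondary outcomes will investigate if the treatment effect of antenatal corticosteroid is influenced by the following variables". Tertiary outcomes are not included.
- **The outcomes.** The 31 July 2024 addendum adds "Components of obesity/overweight outcome" (BMI, height and weight) to the tertiary list, and says of the timing: "This addition was made after all analyses had been completed but before unblinding of treatment groups". In Appendix 15.2, height and weight are the participant's own questionnaire answers. No sex-specific or standardised version is defined.

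**The concern.** Men and women differ greatly in adult height. A model that pools them without a sex term leaves the whole between-sex variance in the residual, and the confidence interval for the treatment difference widens accordingly.

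Three parts of the plan might seem to repair this, but do not:

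- **The marked-imbalance clause.** It brings sex in only when the arms look different. The precision gained from a prognostic covariate does not depend on imbalance, so with balanced arms the loss is left untouched.
- **The sex subgroup analysis.** It stops at secondary outcomes.
- **The maternal random effect.** It models what siblings share. Sex varies between singletons and within unlike-sex multiples.

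What is at stake is the width of the interval. The study hypothesis in section 2 is that there are no long-term adverse impacts, and section 8 says that the sample is capped by the number of participants who could be located. In that setting a needlessly wide interval makes a null result on height less informative than the data allow, and covariate adjustment is one of the few remaining ways to gain precision.

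**Working it through.** **The plan's own figure.** The only power statement (section 8) concerns asthma: 214 participants, 35% against 57% (35 + 22 points, ratio 57/35 = 1.63), 90% power, 5% level, taken as two-sided. With pooled proportion 0.46:

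n per arm = [1.960 × √(2 × 0.46 × 0.54) + 1.282 × √(0.35 × 0.65 + 0.57 × 0.43)]² / 0.22² ≈ 106, or 212 in all.

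With 107 per arm the power is 90.3%, so the figure reproduces. The SAP has no corresponding figure for height, weight or BMI.

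**Inputs for the precision check**

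- From the SAP: 214 consenting participants (section 10, Analysis approach).
- Assumed, because the SAP does not give them: equal arms (at most 107 each), half male, no clustering, and nothing explained by gestational age.
- Assumed sex difference D and within-sex SD s: height D = 11-15 cm, s = 6-7.5 cm; weight D = 8-14 kg, s = 13-19 kg.

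**Formulas**

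- Pooled SD without a sex term: √(s² + D²/4)
- Share of variance explained by sex: (D²/4) / (s² + D²/4)
- 95% half-width: 1.96 × SD × √(2/107), using the pooled SD without sex and s with sex
- Ratio of widths: s / √(s² + D²/4). The number per arm cancels.

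**Worked case for height, D = 13, s = 7**

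- Pooled SD = √(49 + 42.25) = 9.55 cm; share explained = 42.25/91.25 = 46%.
- Half-width without sex: 1.96 × 9.55 × 0.1367 = 2.56 cm. With sex: 1.96 × 7 × 0.1367 = 1.88 cm, which is 27% narrower.
- Equivalent sample multiplier: 91.25/49 = 1.86.
- Power for a 3 cm difference rises from 63% to 88%. The difference detectable with 80% power falls from 3.66 to 2.68 cm.

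**Range**

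| Outcome | D | s | Variance explained | Half-width without / with sex | Narrower by | Sample multiplier |
|---|---|---|---|---|---|---|
| Height, smallest gain | 11 cm | 7.5 cm | 35% | 2.49 / 2.01 cm | 19% | 1.54 |
| Height, largest gain | 15 cm | 6 cm | 61% | 2.57 / 1.61 cm | 38% | 2.56 |
| Weight, smallest gain | 8 kg | 19 kg | 4% | 5.20 / 5.09 kg | 2% | 1.04 |
| Weight, middle | 11 kg | 16 kg | 11% | 4.53 / 4.29 kg | 5% | 1.12 |
| Weight, largest gain | 14 kg | 13 kg | 22% | 3.96 / 3.48 kg | 12% | 1.29 |

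No range was worked for BMI. Sex is expected to explain little of it.

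**Caution on the absolute figures.** Section 5 provides for participants who consented but did not complete the questionnaire, the only source of height and weight, and section 10 rules out imputation. So 107 per arm is an upper bound: the half-widths and powers above are optimistic both with and without sex. The percentage narrowing is unaffected, because n cancels.

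**The case against.** The strongest reply is that little depends on this. The three measures are self-reported, tertiary, added late, and listed as components of an obesity item that itself feeds a cardiovascular risk composite. No primary or secondary estimate rests on them. A randomised comparison without sex remains unbiased in expectation, and its wider interval is honest. All of this stands, and it sets the severity.

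Several stronger readings are tempting, but the SAP does not support them:

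- **That raw means are compared.** The adjusted model includes gestational age and a maternal random effect, and sex can enter if markedly imbalanced. The accurate statement is that sex is not pre-specified.
- **That precision on body size in general is badly lost.** This is true of height only. The weight interval changes modestly and BMI hardly at all.
- **That a known growth harm goes poorly tested.** Section 3 does report: "Z-scores for weight and head circumference at birth were lower in the babies who received repeat corticosteroids". The same sentence adds that the z-scores no longer differed at hospital discharge. Section 3 then reports no significant difference in body size at 2 years and similar body size at 6-8 years. It mentions no length z-score deficit, and nothing names adult height as a harm.
- **That the birth data show unstandardised means to be the less sensitive scale.** The SAP does not say what those z-scores were standardised for. At birth, size also depends on gestational age at delivery, so the contrast between z-scores and means there says nothing about a missing sex term at 20 years.
- **That chance sex imbalance is a further problem.** With D = 13 cm, a one-SD imbalance of √(0.25 × 2/107) = 6.8 percentage points moves the mean height difference by 0.89 cm. The unadjusted standard error (1.31 cm, against 0.96 cm with sex) already contains this: √(1.31² − 0.96²) = 0.89 cm. Counting it separately counts one loss twice.

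**Conclusion.** The point holds as a modest efficiency gap. The covariate list in section 10, applied through section 12, leaves sex out of the height, weight and BMI models unless the arms happen to differ markedly, and no other part of the plan supplies it for these tertiary outcomes. Under the stated assumptions, a sex term would narrow the height interval by about 19-38%, equivalent to roughly 1.5 to 2.6 times the sample. For weight the narrowing is about 2-12%, and for BMI it is probably negligible.

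The percentages rest on assumed sex differences and SDs that the SAP does not give, on an even sex split and on ignoring clustering. The direction does not depend on the exact values: some gain for height follows whenever the sexes differ appreciably relative to the within-sex spread.

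This is an improvement of low severity, not an error that invalidates a result. The asthma outcome and all secondary outcomes are unaffected.

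**What to change.** In section 10 (Covariates and potential confounders), with a matching line in the 31 July 2024 addendum, state that height and weight, and BMI for consistency, are adjusted for sex as a fixed covariate in addition to gestational age at randomisation, whatever the observed balance. Keep the unadjusted mean difference beside it, as section 10 already provides. With an identity link, adding sex leaves the target mean difference unchanged and alters only its precision.

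Timing decides the label. The addendum records that these outcomes were added after the analyses were complete but while groups were still blinded. If groups remain blinded, the sex-adjusted model can be pre-specified. If they are already unblinded, report it as a clearly identified post hoc analysis under section 13.

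The cost is one sentence, one extra term in three models, and one degree of freedom in at most 214 participants. No new data are needed.

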## 13. Exploratory analyses

### Enriched Sample Analysis

Where appropriate, data from outcomes obtained at the 6–8-year follow-up will be added in the outcomes if they are missing at 20-year and the denominators corrected to include the number of participants in each treatment arm for whom data were available at either 6–8-year or 20-year follow up. The feasibility of using the 6–8-year data as a prior in a Bayesian analysis will also be investigated.

### Subgroup analyses

Exploratory analyses for primary and secondary outcomes will investigate if the treatment effect of antenatal corticosteroid is influenced by the following variables:

- Sex
- Socioeconomic status (based on New Zealand Deprivation Index for their area of residence at 20-year follow-up) – most deprived (deciles 8-10) vs other.

Analyses for each of the primary and secondary outcomes listed will be performed with each of these potential subgroups as main and interaction effects (with treatment allocation) and measures of effect will be presented for each of the subgroup strata.

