#### **Tertiary Outcomes:**

- Educational achievement outcomes: no secondary school qualification
- Educational achievement outcomes: any disciplinary action
- Social outcomes: any convictions
- Social outcomes: unemployment
- Social outcomes: alcohol use in the past year
- Social outcomes: recreational drug use
- Social outcomes: past/current smoking (pack years)
- Social outcomes: past/current vaping
- Components of neurodevelopmental disability composite outcome:
  - visual impairment
  - hearing impairment
  - intellectual impairment
  - cerebral palsy
  - epilepsy
  - autism spectrum disorder (including Asperger's syndrome)
  - attention deficit disorder (ADD) or attention deficit hyperactivity disorder (ADHD)
- Components of cardiovascular composite outcome:
  - Hypertension
  - Cardiomyopathies
  - Arrhythmias
  - heart failure
- Components of cardiovascular disease risk factors composite outcome:
  - high blood pressure
  - dyslipidaemia
  - diabetes mellitus
  - obesity/overweight
- Components of diabetes composite outcome:
  - prediabetes/diabetes mellitus
  - gestational diabetes mellitus
- Components of mental health composite outcome
  - depression
  - bipolar affective disorder
  - anxiety disorders
  - suicide/self-harm

- schizophrenia
- Components of functional difficulties outcome
  - Difficulty seeing, even if wearing glasses
  - Difficulty hearing, even if using a hearing aid
  - Difficulty walking or climbing steps
  - Difficulty remembering or concentrating
  - Difficulty washing all over or dressing
  - Difficulty communicating
- Components of obesity/overweight outcome
  - BMI
  - height
  - weight

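### The socioeconomic subgroup is defined by deprivation at the 20-year address, a post-randomisation variable, so its stratum effects may be biased and it cannot be run for death

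*SAP*

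**What the plan says.** SAP section 13 (Subgroup analyses) states the aim as "Exploratory analyses for primary and secondary outcomes will investigate if the treatment effect of antenatal corticosteroid is influenced by" two variables: sex, and "Socioeconomic status (based on New Zealand Deprivation Index for their area of residence at 20-year follow-up". The second is dichotomised as "most deprived (deciles 8-10) vs other".

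The scope is wide: "Analyses for each of the primary and secondary outcomes listed will be performed" with each subgroup variable entered as "main and interaction effects (with treatment allocation) and measures of effect will be presented for each of the subgroup strata". Section 5 lists one primary and 13 secondary outcomes, and death is among the secondary ones. Section 10 (Analysis approach) sets the denominator for death at 352 fetuses alive at randomisation, and at 214 consenting participants for every other outcome.

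Randomisation took place in pregnancy, in "women who remained at risk of preterm birth at less than 32 weeks' gestation" (section 3).

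The tertiary outcomes in section 5 include "Social outcomes: unemployment" and "Educational achievement outcomes: no secondary school qualification". The study hypothesis in section 2 covers social as well as health outcomes in the offspring.

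**The concern.** A subgroup analysis has a causal reading when the subgroup is fixed before allocation, because the arms are then comparable within each stratum. Deprivation at the participant's own address at follow-up is not fixed in that way. The plan itself treats neighbouring social variables (employment, qualifications) as possible results of treatment. The primary outcome counts asthma at any age (Appendix 15.2), so many events will precede the address and could influence it.

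Section 10 (Covariates and potential confounders) limits any additional adjustment to baseline variables. Section 13 does not apply the same restriction to this subgroup. Sex, the other subgroup variable, does not raise the problem.

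At stake are the stratum-specific effects that the plan commits to reporting and, under a further condition, the interaction tests. The plan gives no caveat beyond the exploratory label and no comparison of deprivation between arms.

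**Working it through.** **The plan's own figure.** The SAP gives no power for the subgroup test, only for the primary comparison (section 8): 214 participants, 35% v 57% (RR 1.63), 5% level, 90% power. Assume 107 per arm, a two-sided test and no clustering.

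- Null SE = √(2 × 0.46 × 0.54 / 107) = 0.0681.
- Alternative SE = √((0.35 × 0.65 + 0.57 × 0.43) / 107) = 0.0665.
- Power = Φ((0.22 − 1.96 × 0.0681) / 0.0665) = Φ(1.30) = 90.3%. The stated figure reproduces.

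**Illustration of the bias.** Take asthma as 35% in both arms, so there is no treatment effect. The SAP gives no deprivation rates, so all of those below are assumptions. In the placebo arm 30% are deprived, whatever their asthma status. In the repeat arm 30% of those with asthma and 20% of those without are deprived.

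- Repeat arm, deprived stratum: asthma risk = 0.35 × 0.30 / (0.35 × 0.30 + 0.65 × 0.20) = 0.105 / 0.235 = 0.447. RR = 0.447 / 0.35 = 1.28.
- Repeat arm, other stratum: asthma risk = 0.245 / 0.765 = 0.320. RR = 0.320 / 0.35 = 0.92.
- Ratio of RRs = 0.447 / 0.320 = 1.40 (log 0.333).

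**How often the interaction test would reject.** The variance of the log ratio is the sum over the four arm-by-stratum cells of (1 − p) / (n·p), where n is 107 times the cell's share of its arm:

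0.0492 (repeat, deprived) + 0.0259 (repeat, other) + 0.0579 (placebo, deprived) + 0.0248 (placebo, other) = 0.158, so SE = 0.397.

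Then z = 0.333 / 0.397 = 0.84. The two-sided rejection probability is P(Z > 1.12) + P(Z < −2.80), about 13%, against 5% nominal. The deprived stratum would hold about 25 repeat-arm and 32 placebo participants, with about 11 asthma cases in each arm.

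**Sensitivity to the mechanism** (still no effect on asthma, 107 per arm):

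| Assumed deprivation, placebo → repeat | RR deprived | RR other | Ratio | Rejection |
|---|---|---|---|---|
| 30% → 20%, whatever the asthma status | 1.00 | 1.00 | 1.00 | 5.0% |
| Asthma 35% → 28%; no asthma 28% → 22.4% (both cut by a fifth) | 1.00 | 1.02 | 0.98 | 5.0% |
| Asthma 45% → 35%; no asthma 25% → 15% | 1.13 | 1.03 | 1.10 | 5.8% |
| Asthma 40% → 30%; no asthma 25% in both arms | 0.85 | 1.11 | 0.76 | 10.9% |
| Asthma 45% → 25%; no asthma 25% in both arms | 0.71 | 1.24 | 0.58 | 28.6% |

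A different structure was also simulated, in which an unmeasured cause drives both asthma and deprivation (loadings 0.5 to 0.7) and treatment shifts deprivation. Both stratum RRs then move away from 1.00, to between about 1.04 and 1.24. The ratio stays at 0.97 to 1.01 and rejection stays near 5%. If treatment does not shift deprivation at all, the ratio is 1.00 and rejection is 5.0%.

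**Death and missing index values.** Section 13 applies the subgroup to every secondary outcome, so it covers death among 352. Anyone who died before follow-up has no address at follow-up, so the events are the very records without a stratum. A further difficulty is that 352 − 214 = 138 fetuses lie outside the consenting group, and the plan gives no route to a 20-year address for the survivors among them.

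Eligibility (section 4) depends on the mother having been randomised in New Zealand, not on current residence. Section 3 records that some children randomised there lived elsewhere by 6–8 years. Such participants may have no New Zealand index value. The SAP does not say how many, or how they would be handled.

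**The case against.** The strongest reply is that the analysis is exploratory, the number of tests will be reported, and the primary analysis does not use this variable. That stands, and it limits the consequence. It does not make the strata comparable, because the label speaks to the strength of evidence and not to bias.

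A second reply is that nothing shows treatment changes area deprivation. Listing unemployment and qualifications as outcomes is not evidence of an effect, and the study hypothesis is that there is no long-term adverse impact. This also stands: deprivation at 20 years may lie downstream of treatment, but the SAP does not establish that it does.

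A reader might infer that any effect of treatment on later deprivation makes the interaction test spurious. The calculations do not support that. An equal shift leaves the test at or close to its nominal level, and under a common cause it is the stratum RRs that are biased. The 1.40 example needs treatment to lower deprivation only in people without asthma, and even then the test rejects about 13% of the time.

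**Conclusion.** The concern holds in a limited form. The subgroup variable is measured after randomisation and could be affected by treatment and by earlier health, so the stratum-specific effects are not protected by randomisation and can be biased. Distortion of the interaction test needs the further condition that treatment shifts deprivation unevenly by outcome status. In the scenarios of that kind tried here, rejection was 11% to 29% against 5% nominal. These figures rest on assumed deprivation rates, 107 per arm and no clustering. They show what could happen and do not estimate what will.

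The defect for death needs no such assumptions: the analysis cannot be done as written.

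It would go too far to say that the plan will produce a false claim about who is harmed or helped. The SAP makes no such claim, and the primary conclusion does not depend on this analysis. Severity is minor to moderate.

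**What to change.** Define the socioeconomic subgroup by a maternal measure fixed at or before randomisation, for example deprivation of the address at trial entry with the same decile cut. The SAP does not say whether the trial holds such a measure. If it does, the cost is the linkage work and some missing values.

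If it does not, change the wording of section 13:

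- drop the interaction test on 20-year deprivation;
- report 20-year deprivation by arm;
- present any results by 20-year deprivation as descriptive, not as effect modification;
- exclude death from this subgroup;
- state how participants without an index value are handled, and report their number by arm.

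This fallback needs no new data. It costs one exploratory test per outcome. The sex subgroup can stay as it is.
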